**Allergic reactions:**

For Grade 1 or 2 acute hypersensitivity reactions, no dose modification of oxaliplatin is required if, in the investigator's opinion, it is in the patient's best interest to continue. Pre-medication with dexamethasone 20 mg IV, diphenhydramine 50 mg IV, and one of the following: cimetidine 300 mg IV, ranitidine 50 mg IV, or famotidine 20 mg IV 30 minutes prior to study drug administration is suggested. If an allergic reaction persists into the next cycle, administer 50 mg dexamethasone PO 12 hours and 6 hours prior to administration of oxaliplatin. For Grade 3 or 4 acute hypersensitivity reactions, treatment with oxaliplatin should be discontinued.

**Pulmonary fibrosis:**

In the case of respiratory symptoms indicative of pulmonary fibrosis such as nonproductive cough, dyspnea, crackles, rales, hypoxia, tachypnea or radiological pulmonary infiltrates, oxaliplatin should be interrupted pending further investigation. If interstitial pulmonary fibrosis is confirmed, permanently discontinue oxaliplatin.

### **Neurologic Toxicity Scale – Oxaliplatin Dose**

| TOXICITY                                                                                     | Grade | Duration of Toxicity                                            |                                              |                                              |
|----------------------------------------------------------------------------------------------|-------|-----------------------------------------------------------------|----------------------------------------------|----------------------------------------------|
|                                                                                              |       | 1-7 Days                                                        | > 7 Days                                     | Persistent between cycles                    |
| Paresthesia/dysesthesia that do not interfere with function                                  | 1     | No dose reduction                                               | No dose reduction                            | 75 mg/m                          |
| Paresthesia/dysesthesia, interfering with function, but not activities of daily living (ADL) | 2     | No dose reduction                                               | 75 mg/m                          | Stop treatment until recovery (grade 0 or 1) |
| Paresthesia/dysesthesia with pain or with functional impairment that also interfere with ADL | 3     | 75 mg/m                                             | Stop treatment until recovery (grade 0 or 1) | Stop treatment until recovery (grade 0 or 1) |
| Paresthesia/dysesthesia that are disabling or life-threatening                               | 4     | Top treatment permanently                                       | Top treatment permanently                    | Top treatment permanently                    |
| ACUTE: (during or after the 2-infusion) laryngopharyngeal dysesthesia                        |       | Increase duration of next infusion to 6 hours ± benzodiazepines | Not applicable                               | Not applicable                               |

### **FOLFOX induced Toxicity (other than neurotoxicity)**

#### **Haematological:**

Based on the most severe toxicity experienced since the last treatment, the following dose modifications should be used for haematological toxicities.

FOLFOX is known to increase in the risk of febrile neutropenia (10-20 %), G-CSF may be used depending on the patient risk factors (cf EORTC recommendation <https://www.sciencedirect.com/science/article/pii/S0959804906003911>) .

### **Haematological toxicity scale – Oxaliplatin + 5-FU Dose adjustment**

| TOXICITY                                                                                                                                                                                                                                                                                                                                                                                                                           | Grade | 5-FU bolus     | 5-FU infusion  | Oxaliplatin   |
|-------------------------------------------------------------------------------------------------------------------------------------------------------------------------------------------------------------------------------------------------------------------------------------------------------------------------------------------------------------------------------------------------------------------------------------------|--------------|-----------------------|-----------------------|----------------------|
| Hemoglobin                                                                                                                                                                                                                                                                                                                                                                                                                                | All          | No dose reduce        | No dose reduce        | No dose reduce       |
| Neutropenia b                                                                                                                                                                                                                                                                                                                                                                                                                  | 3            | 200 mg/m  | 200 mg/m  | 75 mg/m  |
| Neutropenia                                                                                                                                                                                                                                                                                                                                                                                                                               | 4            | 0                     | 200 mg/m  | 75 mg/m  |
| Febrile Neutropenia a                                                                                                                                                                                                                                                                                                                                                                                                          | ≥ 3          | 0                     | 200 mg/m  | 75 mg/m  |
| Thrombocytopenia b                                                                                                                                                                                                                                                                                                                                                                                                             | ≥ 3          | 200 mg/m  | 200 mg/m  | 75 mg/m  |
| a Febrile Neutropenia Grade 3=ANC<1.0X10  /L with fever 38.5°C
b Dose reduction to applied at the second occurrence of persisting Grade 2 haematological toxicity leading to an extended rest period of ≥ 2 weeks
Suppress 5FU bolus if neutropenia or thrombocytopenia grade 3-4 occurrence after first dose reduction to 200mg/m 
The dose of leucovorin should remain identical |              |                       |                       |                      |

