**Investigational Product(s), Dose, and Mode of Administration:**

- **Durvalumab**, 750 mg Q2W (equivalent to 20 mg/kg Q4W) for 12 months in patients > 30 kg

- **Tremelimumab** 75 mg Q4W (equivalent to 1 mg/kg Q4W) for up to 4 doses/cycles in patients >30 kg

Weight-based dosing should be utilized for patients <30 kg durvalumab 20 mg/kg Q4 and tremelimumab 1 mg/kg Q4

- **FOLFOX**: Oxaliplatin 85 mg/m^2 (IV, 2h); Folinic acid 400 mg/m^2 or L-Folinic Acid (200mg/m^2) (IV, 2h); 5-FU bolus 400 mg/m^2 (IV, 10 min) ; 5-FU continu 2400 mg/m^2 (IV, 46h)

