### **5.3.2 Product preparation, Doses and treatment regimens administration**

Subjects will be administered with FOLFOX in line with normal clinical practice, with a dose and schedule of Oxaliplatin, 85 mg/m^2 administered as intravenous infusion over 2 hours in 250 ml dextrose 5% or sterile water for injection concurrently (via a Y-connector) with LV, 400 mg/m^2 (400 mg/m^2 for form dl or 200 mg/m^2 for form l) administered as intravenous infusion over 2 hours, in 250 ml dextrose 5%, or sterile water for injection followed by 5-FU, 400 mg/m^2 administered as a bolus injection (intravenous push administered manually in approximately 2 minutes), followed by 5-FU, 2400 mg/m^2 administered as a intravenous infusion over 46 hours. Oxaliplatin should always be administered before fluoropyrimidines.

Dose of oxaliplatin, 5-FU and LV will be administered on the basis of milligrams of each drug per square meter of body surface area (BSA) as measured at baseline (mg/m^2). The dose of oxaliplatin administered should be as close as possible to the calculated dose and will be limited to a maximum BSA of 2.0 m^2. Though the weight of the patient may change throughout the study, BSA will be assumed to stay close to that measured at baseline, i.e. no dose adjustments for changes in body weight will be done unless weight loss alone is considered to be an adverse event of grade 2 or more. Cycle length is 2 weeks comprising approximately 48 hours of infusion and 12 days of rest. It is expected that subjects will receive between 1 and 12 cycles of FOLFOX (6 months).

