### 6.2.3 Toxicity management guidelines for combination treatment regimen

Combination of Durvalumab, tremelimumab and FOLFOX has never been evaluated. Any potential overlapping toxicity may occur following treatment with this combination and will be difficult to assess. Toxicity will not be managed individually but will be managed according to the guidelines described in section 6.2.1 and 6.2.2 and both treatments will be adjusted simultaneously.

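### The haematological dose table sets the 5-FU infusion at 200 mg/m² in all four reduction rows, very probably a dropped zero for 2000 mg/m², and no text corrects it

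*Protocol*

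**What the plan says.** The full infusion dose is stated twice and consistently: "5-FU continu 2400 mg/m 2 (IV, 46h" in the synopsis and "5-FU, 2400 mg/m 2 administered as a intravenous infusion over 46 hours" in section 5.3.2. The full bolus is 400 mg/m² and full oxaliplatin is 85 mg/m².

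Section 6.2.2 has two dose-adjustment tables for toxicity other than neurotoxicity.

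- **Haematological table.** Grade 3 neutropenia and thrombocytopenia of grade 3 or more read "200 mg/m 2 | 200 mg/m 2 | 75 mg/m 2" for bolus, infusion and oxaliplatin. Grade 4 neutropenia and febrile neutropenia of grade 3 or more drop the bolus to 0 and keep the same infusion and oxaliplatin entries. The haemoglobin row requires no reduction.
- **Non-haematological table.** Nausea/vomiting, diarrhoea, stomatitis grade 3, stomatitis grade 4 and skin toxicity all set the infusion at 2000 mg/m². The remaining rows either leave 5-FU unchanged or stop it permanently.

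A footnote to the haematological table reads: "Suppress 5FU bolus if neutropenia or thrombocytopenia grade 3-4 occurrence after first dose reduction to 200mg/m 2". Footnote b, attached to the grade 3 neutropenia and thrombocytopenia rows, begins: "Dose reduction to applied at the second occurrence of persisting Grade 2 haematological toxicity leading to an extended rest period of" and sets that rest period at two weeks or more.

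The table is introduced as an instruction: "the following dose modifications should be used for haematological toxicities". Section 6.2.3 repeats this for the combination: "Toxicity will not be managed individually but will be managed according to the guidelines described in section 6.2.1 and 6.2.2".

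**The concern.** Two tables in one section, with the same columns, give reduced infusion doses that differ tenfold. The lower figure sits in every reduction row of the haematological table. It also sits beside mild steps for the other drugs, so it does not look like a deliberate choice.

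At stake is the first-line backbone chemotherapy. A site that follows the table gives a patient with grade 3 neutropenia about a twelfth of the planned infusion, while a patient with grade 3 diarrhoea keeps five sixths. Footnote b appears to allow the reduction after a second episode of persisting grade 2 toxicity, so the printed cut may not be limited to grade 3–4 events. Figure 1a schedules FOLFOX at visits 1 to 6, and section 11.3.2 evaluates the primary objective at 3 months. An underdose in those cycles would therefore come before the primary evaluation.

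**Working it through.** No sample-size or power figure is involved. The check is a row count and simple dose arithmetic.

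**Inputs.** Full infusion 2400 mg/m² (synopsis, 5.3.2); full bolus 400 mg/m² and full oxaliplatin 85 mg/m² (same places); reduced doses from the two tables in 6.2.2.

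**Row comparison** (mg/m²; "–" is not used, so unreduced oxaliplatin is shown as 85)

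| Table | Row | Bolus | Infusion | Oxaliplatin |
|---|---|---|---|---|
| Haematological | Neutropenia 3 | 200 | 200 | 75 |
| Haematological | Neutropenia 4 | 0 | 200 | 75 |
| Haematological | Febrile neutropenia ≥3 | 0 | 200 | 75 |
| Haematological | Thrombocytopenia ≥3 | 200 | 200 | 75 |
| Non-haematological | Nausea/vomiting ≥3 | 200 | 2000 | 75 |
| Non-haematological | Diarrhoea ≥3 | 200 | 2000 | 75 |
| Non-haematological | Stomatitis 3 | 200 | 2000 | 85 |
| Non-haematological | Stomatitis 4 | 0 | 2000 | 75 |
| Non-haematological | Skin toxicity ≥3 | 200 | 2000 | 85 |

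All four haematological reduction rows carry 200; all five non-haematological 5-FU-reducing rows carry 2000. Nausea/vomiting, diarrhoea and stomatitis 4 match a haematological row in both bolus and oxaliplatin and differ only in the infusion.

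**Size of each step**

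- Infusion as printed: 1 − 200/2400 = 91.7% cut (8.3% of full dose).
- Infusion at 2000: 1 − 2000/2400 = 16.7% cut (83.3% of full dose).
- Bolus, where halved: 1 − 200/400 = 50% cut.
- Oxaliplatin: 1 − 75/85 = 11.8% cut.

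**Total 5-FU per cycle** (full dose 400 + 2400 = 2800 mg/m²)

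| Rows | As printed | Cut | With 2000 | Cut | Printed ÷ with 2000 |
|---|---|---|---|---|---|
| Neutropenia 3, thrombocytopenia | 200 + 200 = 400 | 85.7% | 200 + 2000 = 2200 | 21.4% | 18.2% |
| Neutropenia 4, febrile neutropenia | 0 + 200 = 200 | 92.9% | 0 + 2000 = 2000 | 28.6% | 10.0% |

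**Search for a correction.** The footnote on suppressing the bolus ties 200 mg/m² to the bolus, which supports a dropped zero in the infusion column. It does not restate the infusion dose, and no other text in the protocol explains or corrects it.

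**The case against.** The strongest reply is that this is an obvious misprint with little practical force. The tables cover different toxicities, so no single event is assigned two doses. The protocol also points strongly to 2000: the full dose is 2400, the companion table prints 2000 five times, the bolus and oxaliplatin steps match, and the footnote links 200 to the bolus. FOLFOX is a marketed regimen supplied by the sites and given according to normal practice, so a pharmacist could well query a 46-hour infusion at 8% of dose. The error runs toward underdosing rather than added toxicity.

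Most of this stands, and it lowers the chance of harm. It does not remove the defect: these are inferences, and the only explicit instruction for haematological toxicity is the printed figure. A digit lost in converting the table to text cannot be wholly excluded, but it is unlikely to have struck the same column in four cells while the companion table came through intact.

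Three stronger readings are tempting, and the document does not support them:

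- **A count of affected patients.** The text says "FOLFOX is known to increase in the risk of febrile neutropenia (10-20" per cent). Applied to 57 patients, that would give 5.7 to 11.4 for the febrile neutropenia row alone. But the sentence is loosely worded and gives no time base, and G-CSF is allowed. The other three rows have no stated frequency.
- **Actual underdosing.** Nothing shows that any patient received 200 mg/m².
- **A ruling on FOLFOX duration.** Figure 1a, section 5.2.2 and section 5.3.2 disagree on how long FOLFOX is given. Choosing among them sets chemotherapy exposure, so that is a separate matter for the sponsor and not part of this correction.

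**Conclusion.** The point holds as a very probable misprint in an operative dosing rule. The infusion entry in all four haematological reduction rows is a tenth of the figure used throughout the companion table: a 91.7% cut against 16.7%. Followed as written, it leaves 400 or 200 mg/m² of 5-FU per cycle in place of 2200 or 2000.

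That 2000 mg/m² was intended is an inference from the matching steps and the footnote; only the sponsor can confirm it. The tenfold difference and the absence of an explicit correction rest on no assumption beyond the table being reproduced faithfully. The entry should be corrected because it governs backbone chemotherapy, but no design parameter, sample size or Simon boundary depends on it.

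**What to change.** 1. The sponsor confirms the intended reduced infusion dose.
2. On confirmation, a clarification letter or amendment changes the infusion column to 2000 mg/m² in the rows for neutropenia 3, neutropenia 4, febrile neutropenia ≥3 and thrombocytopenia ≥3 in section 6.2.2.
3. The FOLFOX dispensing logs required by section 5.3.4 are checked for every patient already reduced for haematological toxicity, to see which infusion dose was given.

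The cost is one letter or amendment and a log check at the sites.

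### The haematological FOLFOX table sets the reduced 5-FU infusion at 200 mg/m2, 8% of full dose, where the companion table has 2000 mg/m2; a dropped zero is the likely cause

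*Protocol*

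**What the plan says.** The Synopsis ("5-FU continu 2400 mg/m 2 (IV, 46h") and section 5.3.2 ("2400 mg/m 2 administered as a intravenous infusion over 46 hours") agree on the full infusional dose. The full bolus is 400 mg/m2 and full oxaliplatin is 85 mg/m2.

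Section 6.2.2 then sets reductions in two tables. The text introducing the haematological one says "the following dose modifications should be used for haematological toxicities". Its haemoglobin row changes nothing. Its other four rows all reduce dose: neutropenia grade 3, neutropenia grade 4, febrile neutropenia grade 3 or higher, and thrombocytopenia grade 3 or higher. The grade 3 neutropenia and thrombocytopenia rows read "200 mg/m 2 | 200 mg/m 2 | 75 mg/m 2" for bolus, infusion and oxaliplatin. The other two rows have a bolus of 0 with the same infusion and oxaliplatin doses.

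A note under the table adds: "Suppress 5FU bolus if neutropenia or thrombocytopenia grade 3-4 occurrence after first dose reduction to 200mg/m". There the 200 mg/m2 level belongs to the bolus.

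The non-haematological table reduces the infusion in five rows (nausea or vomiting, diarrhoea, stomatitis grade 3, stomatitis grade 4, skin toxicity). Each of the five gives 2000 mg/m2.

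**The concern.** A 200 mg/m2 infusion is one twelfth of full dose. It stands beside a bolus that is halved or stopped and an oxaliplatin dose that is only slightly trimmed. That scheme is not coherent, because the infusion carries most of the 5-FU in this regimen. The infusion cell repeats the figure that the note attaches to the bolus. It also differs by exactly a factor of ten from the infusion cell in otherwise identical rows of the companion table.

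This table governs treatment. A site that follows it would nearly remove infusional 5-FU from a patient on first-line treatment for metastatic disease after one of these events, with oxaliplatin almost unchanged. A pharmacy might query the value, but the protocol states no other haematological figure. A site that departs from the table deviates from the protocol, and the 9 sites could resolve the matter differently.

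**Working it through.** **Inputs.** Full doses (Synopsis and section 5.3.2): infusion 2400, bolus 400, oxaliplatin 85 mg/m2. Full 5-FU per cycle: 400 + 2400 = 2800 mg/m2. Reduced doses come from the two tables in section 6.2.2.

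**Rows matched on bolus and oxaliplatin** (mg/m2: bolus / infusion / oxaliplatin):

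| Haematological row | As printed | Matching non-haematological row | As printed |
|---|---|---|---|
| Neutropenia 3; thrombocytopenia ≥3 | 200 / 200 / 75 | Nausea or vomiting ≥3; diarrhoea ≥3 | 200 / 2000 / 75 |
| Neutropenia 4; febrile neutropenia ≥3 | 0 / 200 / 75 | Stomatitis 4 | 0 / 2000 / 75 |

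Only the infusion cell differs within each pair. Stomatitis 3 and skin toxicity also reduce the infusion to 2000 mg/m2, but they leave oxaliplatin unreduced, so they are not used as matches.

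**Fraction of full dose kept** (reduced dose divided by full dose):

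- Infusion as printed: 200 / 2400 = 8.3%, a cut of 91.7%.
- Infusion in the non-haematological table: 2000 / 2400 = 83.3%, a cut of 16.7%.
- Bolus where reduced: 200 / 400 = 50%.
- Oxaliplatin: 75 / 85 = 88.2%.

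**Total 5-FU per cycle** (bolus plus infusion, divided by 2800):

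| Bolus | Infusion 200 (as printed) | Infusion 2000 |
|---|---|---|
| 200 | 200 + 200 = 400, or 14.3% | 200 + 2000 = 2200, or 78.6% |
| 0 | 0 + 200 = 200, or 7.1% | 0 + 2000 = 2000, or 71.4% |

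**Consistency with the note.** The note makes stopping the bolus the next step after reducing it to 200 mg/m2. With an infusion of 2000, that step takes total 5-FU from 2200 to 2000 mg/m2, a graded reduction. With an infusion of 200, it takes the total from 400 to 200 mg/m2, when most of the drug has already gone.

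**How often the table could apply.** The section offers one figure: "FOLFOX is known to increase in the risk of febrile neutropenia (10-20" per cent). If that range is assumed to be a per-patient risk in this trial, 0.10 × 57 = 5.7 and 0.20 × 57 = 11.4, so about 6 to 11 patients in the febrile neutropenia row alone. This is an illustration and not an estimate.

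**The case against.** The discrepancy and the ratios are not in dispute. The strongest contrary case is about weight, and parts of it stand.

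- **The error is recognisable.** Section 5.3.2 has FOLFOX given as in normal practice, the note links 200 mg/m2 to the bolus, and the companion table shows 2000. A pharmacist therefore has grounds to question the cell. That is true, but grounds to query are not a stated dose, and the general wording on normal practice does not override a specific reduction table.
- **The tables cover different toxicities.** The non-haematological value suggests 2000 mg/m2 for haematological events but does not prove it. This stands: the issue is an unexplained inconsistency, not two rules for one event, and the dropped zero is an inference.
- **The table was read by machine.** A reading error repeated in four cells, beside a companion table that reads 2000, is unlikely. The source page should still be checked.
- **Reach is limited.** A second note (b) qualifies the trigger in the grade 3 neutropenia and thrombocytopenia rows. G-CSF is allowed. Section 6.2.2 bases changes for isolated laboratory values on counts at the start of a cycle. The schedule marks FOLFOX at the first six visits only, although section 5.3.2 allows up to 12 cycles. Late events affect few or no remaining cycles. All of this stands, and it makes the 6 to 11 illustration weak evidence.
- **Direction and timing.** The literal error underdoses; it does not overdose. Version 4.1 is dated January 2020 with last visit planned by Q2 2020, so few patients may still be on FOLFOX apart from retreatment. This shifts the value of the remedy towards the dosing-record check.

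None of this supplies a reason for the printed value.

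**Conclusion.** The concern holds. Four cells of a dosing table that sites are told to use keep 8% of the infusion, where the matching rows of the companion table keep 83%. Taken literally, total 5-FU per cycle falls to 14% or 7% of full dose instead of 79% or 71%, with oxaliplatin at 88%.

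That the figures disagree without explanation is certain on the text as read. That the cause is a lost zero, and that 2000 mg/m2 was intended, is likely and needs the sponsor's confirmation. The number of patients affected is not established. No effect on the 3-month response count, the sample size or the error rates is claimed. The point must be fixed because a tenfold discrepancy in a chemotherapy dose bears directly on individual patients.

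**What to change.** Check the source page and have the sponsor confirm the intended dose. Then change the 5-FU infusion entry to 2000 mg/m2 in the four reducing haematological rows, in line with the non-haematological table. If another value was meant, state it and give the reason.

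Send one dosing clarification to the 9 sites. Review the dosing records of every patient already reduced under this table, including any retreated with FOLFOX, to see which infusion dose was given.

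The cost is four cells in an amendment, one letter and a limited record check. There is no statistical cost.
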